#### Primary Outcomes

Primary outcomes are caregiving representations, assessed through a self-report questionnaire and a narrative interview, and caregivers' parental mentalization, assessed through a self-report questionnaire, and from caregiver language during a narrative interview and observed caregiver-child interaction.

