##### Composite caregiving questionnaire

The CCQ was developed to evaluate primary COS-P outcomes; specifically, components of caregivers' self-reported caregiving representations and parental mentalization. With a view to keeping the questionnaire brief and minimizing repetition, subscales from several validated questionnaires were combined, with their authors' permission. The original rating scales were retained for each subscale. In prior research using the original measures, subscale totals have commonly been reported in addition to (and sometimes, instead of) overall totals. Following initial development, three study sites (sites 1, 2, and 3) piloted the CCQ with COS-P group participants. Feedback from participants, clinicians and service managers led to wording refinements including replacement of “mother” or “parent” with “caregiver,” and providing simpler explanations for some words and phrases that may be unfamiliar to non-native-English speakers. The final study version of the CCQ has 43 items, incorporating:

12 items from two subscales of the tool to Measure Parenting Self-Efficacy (TOPSE)^1^ (49), scored on a 10-point scale, exploring:
– empathy and understanding (six items; e.g., *I understand my child's needs*), and– emotion and affection (six items; e.g., *I am able to show affection to my child*)six items from the parenting questionnaire used in the Longitudinal Study of Australian Children (LSAC) (50), exploring:
– hostile parenting (five items; e.g., *When this child cries, he/she gets on my nerves*) scored on a 10-point scale– parent overall rating of child difficultness (from the Australian Temperament Project (51)); single item; *Compared to the average child, do you think your child is…*) scored on a 5-point scale, ranging from *Much less difficult* to *Much more difficult*seven items from the Caregiving Helplessness Questionnaire (Mother Helpless subscale, CHQ (52)); e.g., *When I am with my child, I often feel out of control*) scored on a 5-point scalethe full 18-item Diamond Maternal Reflective Functioning Scale [DMRFS; (53); e.g., *I think about what my child may be thinking or feeling*] scored on a 4-point scale

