##### The circle of security interview

Augmenting the CCQ, the Circle of Security Interview [COSI; (9)] will enable a more in-depth assessment of caregiving representations. The COSI is based on two widely validated instruments to assess attachment and caregiving representations, respectively, the Adult Attachment Interview (AAI) (54); and the Parent Development Interview (PDI) (55). The COSI forms part of the 20-week COS-I treatment protocol, and differs from the two source measures by including direct questions to the parent about their experience of the Strange Situation Procedure (SSP). The final question asks the caregiver what they hope the target child learns from being parented by them. Like the AAI and the PDI, the COSI is a narrative interview, designed to “surprise the unconscious” [(54), p. 19], and is thus less prone to response bias than a questionnaire.

In the current study, the questions related to the SSP will be omitted. Interviews will be audio recorded and transcribed, and de-identified transcripts will be used for coding. Responses to the questions exploring perceptions of self in the caregiving role and relationship with the target child will be coded using a coding system developed by [name] and colleagues (16). This eight-scale system comprises two affect dimensions, reflecting the caregiver's feelings about the child and/or their relationship, and six dimensions reflecting the caregiver's self-perception in the caregiving role (16). The system shows promising validity, with theoretically expected associations between one subscale (“weak”) and observed dimensions of attachment (negatively correlated with attachment security and positively with attachment disorganization) (16) and between the total representations score and parental mentalizing (positive correlation with appropriate mind-related comments) (56).

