### Sample Size Calculation

Power analyses were conducted using G^*^Power 3.1 (70). Based on preliminary CCQ data for the first 67 intervention group participants, a total sample size of 128 was indicated to detect a medium intervention effect with 80% power and an error level of 0.005 (for multiple comparisons). Assuming an attrition rate of 20%, we aim to recruit a total of 154 participants to complete study questionnaires. Sample size for the interview and observational study measures was calculated based on analysis of data from the COSI interview in a previous comparable study (16). While there was a large intervention effect on caregiving representations in that study, it is estimated the effect size will be smaller in the current study given the shorter duration and lower intensity of the intervention. To detect a medium effect size with 95% power and an error level of 0.05, assuming a Time 1–Time 2 correlation of 0.5, a sample size of 40 was indicated. Assuming an attrition rate of 20%, we aim to include a subsample of 48 participants completing interview and observational study measures (COSI and/or videotaped caregiver-child interaction) in addition to questionnaires.

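### Outcomes named together as primary are sized at two error levels without explanation: 0.005 for the questionnaires, an unadjusted 0.05 for the interview and video measures

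*Protocol article*

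**What the plan says.** Under Primary Outcomes, the article puts both constructs and all their measures in one tier: "Primary outcomes are caregiving representations, assessed through a self-report questionnaire and a narrative interview", with parental mentalization taken from a questionnaire "and from caregiver language during a narrative interview and observed caregiver-child interaction". The tier is not ranked there.

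Under Sample Size Calculation, two calculations stand in one paragraph.

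- Questionnaires: the level is "an error level of 0.005 (for multiple comparisons"). With 80% power for a medium effect, the total comes to 128.
- Interview and observational measures: "To detect a medium effect size with 95% power and an error level of 0.05", with a Time 1 to Time 2 correlation of 0.5, giving 40 participants.

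Only the first is said to allow for multiple comparisons. The Data Analysis section gives no significance threshold that would bring the two together.

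The subsections on the Circle of Security Interview (COSI) and on mind-mindedness describe those measures as adding to the CCQ. Both subsections nevertheless stand under the Primary Outcomes heading.

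**The concern.** The authors recognise that several primary tests call for a stricter level, and then apply it to only part of the primary tier. The part left at 0.05 is also not a single test. It holds at least a COSI representations score and two mind-mindedness scores, one from the interview and one from the video.

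If the sizing levels carry over to testing, each interview or video primary is ten times as likely as a questionnaire primary to be positive by chance (0.05 / 0.005 = 10). Those tests rest on a small subsample of people who agreed to the extra measures and could complete them in time. A chance finding there could be reported as a primary result of the study. In addition, the 95% power stated for the subsample applies only at the unadjusted level.

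**Working it through.** **Inputs from the article.** Levels 0.005 and 0.05; subsample N = 40; correlation 0.5; stated power 95%; two groups and two time points, analysed by mixed design ANOVA.

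**Assumptions.**
- The sizing levels are also the testing levels.
- Tests are independent.
- There are six CCQ scores: two TOPSE subscales, hostile parenting, child difficultness, caregiving helplessness, and the reflective functioning scale.
- There are three interview or video scores: COSI total, representational mind-mindedness, observational mind-mindedness.
- The two groups are of equal size.

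**1. The plan's own figure of 40.** For the group-by-time interaction in a repeated-measures ANOVA with m = 2 time points, the noncentrality is λ = f² × N × m / (1 − ρ), with 1 and N − 2 degrees of freedom.

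- With f = 0.25 (the usual medium value), ρ = 0.5 and N = 40: λ = 0.0625 × 40 × 2 / 0.5 = 10. Power at 0.05 is 87%, and 95% needs N = 54.
- With f = 0.295: λ = 0.0870 × 40 × 2 / 0.5 = 13.9. Power at 0.05 is 95%.

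The stated 40 is therefore returned by an f of about 0.295 but not by 0.25. The article does not give its f, so both values are carried forward.

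**2. Family error under the two levels.**

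| Family | Formula | Result |
|---|---|---|
| Six CCQ scores at 0.005 | 1 − 0.995⁶ | 3.0% |
| Three interview/video scores at 0.05 | 1 − 0.95³ | 14.3% |
| All nine, split levels | 1 − 0.995⁶ × 0.95³ | 16.8% |
| All nine at 0.005 | 1 − 0.995⁹ | 4.4% |

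**3. Where the expected false positives lie.** Questionnaires: 6 × 0.005 = 0.030. Interview and video: 3 × 0.05 = 0.150. The interview and video share is 0.150 / 0.180 = 83%. With only one interview or video test it is 0.050 / 0.080 = 62.5%. It falls below half only if questionnaire tests outnumber the others by more than ten to one. Correlation between tests lowers the family error but leaves this share unchanged.

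**4. Subsample power if 0.005 applied throughout (N = 40, ρ = 0.5).**

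| f | λ | Power at 0.05 | Power at 0.005 |
|---|---|---|---|
| 0.25 | 10.0 | 87% | 58% |
| 0.295 | 13.9 | 95% | 77% |

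To keep 95% power at 0.005 the interaction would need N = 84 at f = 0.25, or 62 at f = 0.295.

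**The case against.** The strongest reply is that both levels appear only in a power calculation. The article sets no testing threshold, and an analysis plan not shown here could apply one rule to all primaries. That stands as a limit on the error rates, which are conditional. It does not remove the inconsistency: two calculations for outcomes of the same tier, side by side, use different levels, and only one is described as allowing for multiplicity. For the same reason, the lack of a stated success rule is not part of this point.

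A second reply is that the COSI and mind-mindedness are described as additions to the CCQ, which hints at a ranking. That wording makes relabelling easy, but it does not cancel the explicit primary label.

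A third is that the study is non-randomized and the authors say openly that it cannot close the evidence gap. That tempers the consequence but does not settle which level applies.

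Four stronger readings are tempting and are not supported:

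- **A family error of 40% or more.** A reader might count all COSI scales as separate primaries, since "This eight-scale system comprises two affect dimensions" and six more. The article names the construct as the outcome and also mentions a total representations score. It does not declare eight primary tests.
- **A correction built for ten tests.** 0.05 / 0.005 = 10, but the article gives neither a divisor nor a method. A level stricter than six or seven scores require would in any case be conservative.
- **A collapse of power from 34% to 10%.** These are the N = 40 figures for a between-group difference of d = 0.5 on change. Most of that shortfall comes from a different definition of a medium effect, not from the error level.
- **That 0.005 was never used.** A two-sample t-test with d = 0.5 and 80% power needs 128 at two-sided 0.05 and 218 at 0.005. This is a separate question and is not settled here, because the preliminary CCQ inputs and the type of test are not reported.

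**Conclusion.** The point holds as an inconsistency in what the article states: one primary tier, two error levels, no explanation. If the sizing levels are the testing levels, and with the test counts and independence assumed above, family error is about 3% for the questionnaires, 14% for the interview and video measures and 17% overall. The finding that most of the risk lies in the subsample does not depend on the exact counts; the percentages do. Correlated tests would bring the family error down.

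The stated 95% power cannot be carried over to a corrected level. At 0.005 it is about 58% to 77%, depending on the effect size assumed. This should be put right before analysis, because it decides how a single positive interview or video result may be reported.

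**What to change.** Choose one of two changes.

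1. **Keep all outcomes primary.** Name one score per measure (each CCQ subscale, the COSI total, representational mind-mindedness, observational mind-mindedness) and apply one error-rate rule across them, for example Holm at an overall 0.05. State the level used for each sample size and restate the subsample power at that level.
2. **Relabel.** Call the interview and video outcomes supportive rather than primary, which is close to how their own subsections already describe them, and report them without a primary claim.

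Either change is a matter of wording in the outcome, sample size and analysis sections. The cost of the first is a less favourable stated power for the subsample. No extra participants are needed if that is accepted. Holding 95% power at 0.005 would take about 62 to 84 completers in place of 40. The cost of the second is that the interview and video results carry less weight.

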### Data Analysis

Given that this is not a randomized trial, an intention to treat analysis is not essential. To maximize understanding of what works for whom, we seek to measure the intervention effect on those participants who actually receive the intervention—and we also seek to understand the factors that influence completion and non-completion of COS-P, as well as variations in response (71). Thus, data in this study will primarily be analyzed to measure the treatment effect on participants who received COS-P as intended. Complete Time 1 and Time 2 data for study participants who attend at least six of the eight COS-P sessions will be included in these analyses, together with data from clinical files and information collected during facilitator fidelity interviews, if appropriate. For participants who (a) attend 5 or fewer COS-P sessions and/or (b) do not complete Time 2 measures, treatment effect will not be measured; only Time 1 data, clinical file data and information collected during facilitator fidelity interviews will be analyzed, to explore whether characteristics of these caregivers distinguish them from completers and/or influence failure to complete the intervention.

Analyses will be conducted using SPSS Version 26 (72). Descriptive analyses will be used to profile and compare the characteristics of the treatment and waitlist control groups in the four participating sites. Bivariate correlations and independent samples *t-*tests will be used to explore relationships among the outcome variables and any potential covariates. As group allocation is not randomized, and recruitment is undertaken across four sites with different characteristics, the two groups may differ on distribution of demographic and risk factors which may impact on intervention effects. Baseline comparability will be assessed using independent samples *t*-tests (for continuous variables) and chi-square tests of independence (for categorical variables). Mixed design ANOVA will be used to control for any observed differences in baseline characteristics. Due to anticipated differences among participant cohorts from the four different sites, child age and depression symptoms (EPDS score at Time 1) will be included as *a priori* covariates. If sample size and composition allow, results will be stratified by site.

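### The 20% attrition allowance is applied by multiplying by 1.2 rather than dividing by 0.8, so targets of 154 and 48 fall slightly short of the required 128 and 40

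*Protocol article*

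**What the plan says.** The Sample Size Calculation section of the protocol article makes two calculations. For the questionnaires, "a total sample size of 128 was indicated to detect a medium intervention effect with 80% power and an error level of 0.005"; then "Assuming an attrition rate of 20%, we aim to recruit a total of 154 participants to complete study questionnaires". For the interview and observational measures, with a medium effect, 95% power and an error level of 0.05, "assuming a Time 1–Time 2 correlation of 0.5, a sample size of 40 was indicated"; then "Assuming an attrition rate of 20%, we aim to include a subsample of 48 participants completing interview and observational study measures".

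The Data Analysis section says who counts towards those numbers. On inclusion, with reference to the effect analyses: "Complete Time 1 and Time 2 data for study participants who attend at least six of the eight COS-P sessions will be included in these". On exclusion, for participants who "attend 5 or fewer COS-P sessions and/or (b) do not complete Time 2 measures, treatment effect will not be measured". Their baseline and clinical-file data are used only to describe how they differ from completers.

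**The concern.** An attrition rate is a proportion of the people recruited. To finish with n analysable participants after losing a fraction d, one recruits n/(1 − d). Recruiting n × (1 + d) is a common shortcut that always gives too few, because the loss then applies to the inflated number and not to n. Both targets look like the product of that shortcut.

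At stake is whether the plan delivers the sample sizes it says it needs when everything goes as assumed: full recruitment and exactly 20% loss. Participants without Time 2 data, and treated participants below six sessions, are left out of the effect analysis, so those losses come straight off the analysed number.

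**Working it through.** **Inputs**, all from the Sample Size Calculation section: required n = 128 (power 80%, error level 0.005) and n = 40 (power 95%, error level 0.05); attrition d = 0.20 for both; targets 154 and 48.

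**Step 1: reproduce the stated targets.**
- n × (1 + d): 128 × 1.2 = 153.6, rounded up to 154; 40 × 1.2 = 48. Both match.
- n / (1 − d): 128 / 0.8 = 160; 40 / 0.8 = 50. Neither equals the stated target.

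The stated targets therefore come from multiplication by 1.2, used twice.

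**Step 2: apply the stated loss to the stated targets.**
- 154 × 0.8 = 123.2, about 123 analysed: 5 short of 128.
- 48 × 0.8 = 38.4, about 38 analysed: 2 short of 40.

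**Step 3: the loss the targets can bear.**
- 1 − 128/154 = 0.169, or 16.9%.
- 1 − 40/48 = 0.167, or 16.7%.

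**Step 4: cost in power.** The section gives neither a numerical effect size nor the G*Power test used. I therefore take the stated power as exactly met at 128 and 40 and scale by the square root of the sample size (two-sided normal approximation): power = Φ[(z for error level + z for power) × √(n analysed / n required) − z for error level].
- Questionnaires: (2.807 + 0.842) × √(123/128) − 2.807 = 3.649 × 0.9803 − 2.807 = 0.770, so power is about 78% against 80%.
- Subsample: (1.960 + 1.645) × √(38/40) − 1.960 = 3.605 × 0.9747 − 1.960 = 1.554, so power is about 94% against 95%.

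**Step 5: check on the corrected targets.** 160 × 0.8 = 128 and 50 × 0.8 = 40.

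**The case against.** The strongest reply is that this hardly matters. The shortfall is 5 of 128 and 2 of 40, worth 1 to 2 percentage points of power. It disappears if attrition is about 16.7% or less. Both targets are worded as aims, not caps, in a non-randomized study that enrols eligible registrants over 18 to 24 months. All of this stands, and it limits the weight of the point. It does not make the arithmetic right: the section states a loss rate and a target that do not fit together.

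Two stronger readings are tempting, and the document supports neither.

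- **A large loss of power.** A reader who assumes a two-sample t-test with d = 0.5 at error level 0.005 finds power of about 47% at 123 analysed. One who assumes a within-between interaction with f = 0.25 and correlation 0.5 finds about 85% at 38. It would be wrong to blame the attrition formula for the distance from 80% and 95%. Under the same assumptions power is already 49.1% at 128 and 86.9% at 40, so the formula again costs only about 2 points. The rest is a separate question about the base sizes, and it depends on a test and an effect size that the section does not give.
- **A larger shortfall because of the six-session rule.** A reader might infer that attendance below six sessions comes on top of the 20%. The section does not define attrition. The Intervention section defines completion as at least six sessions, so the 20% may already include low attendance. This is something to clarify, not a second error.

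**Conclusion.** The point holds and is wrong as written, but small. With the stated 20% attrition and full recruitment, the targets leave about 123 and 38 analysable participants where the plan requires 128 and 40. That costs about 2 points of power for the questionnaires and about 1 for the subsample. The shortfall in numbers rests only on the document's own figures and on its exclusion of non-completers from the effect analysis. The power figures also assume that the stated power is met at 128 and 40, and they use a normal approximation. No analysis rule is affected, and nothing here shows that 128 or 40 is itself right or wrong.

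**What to change.** Any one of these changes to the Sample Size Calculation section would make it consistent:

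- Keep 154 and 48, and state that 20% attrition leaves about 123 and 38 analysed, with about 78% and 94% power on the assumption that the stated power holds at 128 and 40.
- Keep 154 and 48, and state that they allow for about 17% attrition.
- Restate the targets as 160 and 50.

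The first two need only a change of wording. The third needs at most 6 more questionnaire participants and 2 more in the subsample. Optionally, add a sentence saying whether the 20% includes treated participants who attend fewer than six sessions as well as those without Time 2 data.

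### Forty participants do not give the stated 95% power for a conventional medium effect on the interview and observation measures: about 87% at f = 0.25, and about 34–43% for a 0.5 SD between-arm difference in change

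*Protocol article*

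**What the plan says.** The Sample Size Calculation section names the software ("Power analyses were conducted using G^*^Power 3.1 (70") and treats the interview and observation measures separately from the questionnaires. It notes a large effect on caregiving representations in an earlier study of the longer intervention and expects a smaller one here. The target is then "To detect a medium effect size with 95% power and an error level of 0.05", and "assuming a Time 1–Time 2 correlation of 0.5, a sample size of 40 was indicated". After an allowance for 20% attrition, "we aim to include a subsample of 48 participants completing interview and observational study measures". The section gives no value of f or d for medium, no test and no allocation ratio.

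Other sections supply the setting. Design sets two groups assessed at two time points. The Current Study hypothesises more improvement with the programme than on the waitlist. Data Analysis names a mixed design ANOVA. The interview is not peripheral: "Primary outcomes are caregiving representations, assessed through a self-report questionnaire and a narrative interview".

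**The concern.** A reader who enters the printed power, alpha and correlation in G*Power with the usual medium effect does not get 40. There is also a question of scale. The hypothesis concerns a difference between arms in improvement. In a two-by-two mixed design, an f that is conventionally called medium is a large difference between arms when expressed in SD units.

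The interpretation of a null result is at stake. If the interview or observation measures show no effect, the printed 95% invites the conclusion that a medium benefit has been all but excluded. If the true power for a 0.5 SD benefit is below one half, that conclusion would be wrong.

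**Working it through.** **Inputs from the protocol article.** Alpha 0.05, power 95%, correlation ρ = 0.5, N = 40 analysed and 48 recruited, 20% attrition (Sample Size Calculation); k = 2 groups and m = 2 times (Design); mixed design ANOVA (Data Analysis).

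**Assumptions, not in the article.** Medium is taken as f = 0.25 on the ANOVA scale or d = 0.5 on the two-group scale. Tests are two-sided. Allocation is 20 + 20, the most favourable split; unequal arms lower the power.

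**Step 1: try to reproduce 40.** For the group-by-time interaction, G*Power's default uses λ = f²·N·m/(1 − ρ), with 1 and N − 2 degrees of freedom. With m = 2 and ρ = 0.5, λ = 4·f²·N.

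| f | N | λ | Power |
|---|---|---|---|
| 0.25 | 38 | 9.5 | 85.1% |
| 0.25 | 40 | 10.0 | 86.9% |
| 0.25 | 48 | 12.0 | 92.4% |
| 0.25 | 54 | 13.5 | 95.0% |
| 0.30 | 38 | 13.68 | 94.9% |
| 0.30 | 40 | 14.4 | 95.9% |

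At f = 0.25 the answer is 54. A two-sided paired test with dz = 0.5 also needs 54, and a one-sided one 45. The one-sided equivalent of the interaction needs 46, the between-group main effect 158, and G*Power's 'as in SPSS' effect-size option 212. None gives 40 for this design. Two changes do: f = 0.30, or f = 0.25 with a correlation of about 0.65. The second contradicts the stated 0.5.

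**Step 2: attrition.** 48 = 40 × 1.2. Losing 20% of 48 leaves 48 × 0.8 = 38.4, so about 38; keeping 40 would need 40/0.8 = 50. At 38 the power for f = 0.25 is 85.1%.

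**Step 3: put f on the scale of the hypothesis.** An interaction effect f moves each of the four cells by ±f SD. One arm therefore changes by 2f SD in one direction and the other arm by 2f SD in the opposite direction, so the difference in change is 4f SD. The SD of a change score is SD·√(2(1 − ρ)), which equals SD at ρ = 0.5.

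- f = 0.25: 4 × 0.25 = 1.0 SD
- f = 0.30: 4 × 0.30 = 1.2 SD

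As a check, a two-sample t-test on change with d = 1.0 and 20 + 20 has noncentrality 1.0 × √(20/2) = 3.162, whose square is 10.0. That is the λ of Step 1 at N = 40, and the power is the same 86.9%.

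**Step 4: power for a 0.5 SD difference in change, 20 + 20.**

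- Change score (equivalent to the mixed-ANOVA interaction): noncentrality 0.5 × √10 = 1.581, 38 degrees of freedom, power 33.8%.
- Baseline-adjusted: residual SD = √(1 − 0.25) = 0.866 SD, effective d = 0.5/0.866 = 0.577, noncentrality 1.826, power 42.9%.
- With 19 + 19, after attrition from 48: 32.3% and 41.0%.
- For 95% power, the totals would be 210 (change score) or 158 (baseline-adjusted).

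**The case against.** The strongest objection is that the article never says f = 0.25. The calculation is said to rest on interview data from the earlier study, scaled down by judgement, so the figure entered need not be the textbook one. With f = 0.30 the same routine returns exactly 40. This stands in part: a reader might infer that 40 is a proven arithmetic slip, and the article does not support that, because 54 follows from a convention and not from a printed input. It does not rescue the sentence, however. An f of 0.30 is above the conventional medium and amounts to a 1.2 SD difference in change, which sits badly with the section's own expectation of an effect smaller than an earlier large one.

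It can also be said that d = 0.5 between arms is the reviewer's metric and not the article's. That is fair: 158 and 210 answer a different definition of medium and do not contradict a printed number. But the hypothesis is a between-arm one, so a reader needs the power on that scale.

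Three stronger readings are tempting and go beyond the text.

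- A reader might infer that many primary interview scales will each be tested at 0.05 with heavily inflated error. The alpha in a sample-size paragraph does not fix the testing rule, and the article also mentions a total representations score.
- The wording "COSI and/or videotaped caregiver-child interaction" might suggest that each measure will fall well short of 40. No overlap between the two is given, so no shortfall can be calculated.
- The questionnaire target of 128 might seem to prove that medium is used in two senses. That figure has a different alpha and power and rests on preliminary data that are not shown, so the comparison cannot settle the matter.

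**Conclusion.** The point holds as a misstatement of power. Under neither conventional meaning of medium do 40 participants give 95% power for the comparison that the study hypothesises. At f = 0.25 the power is about 87% (about 85% with 38), and 95% needs 54. For a 0.5 SD between-arm difference in change it is about 34% by change score and about 43% with baseline adjustment. The printed 95% is reached only at about f = 0.30, a difference in change of 1.2 SD.

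These figures rest on two-sided alpha 0.05, correlation 0.5 and equal arms. Which effect size was actually entered is unknown, so the defect lies in the unstated effect and the power attached to the word medium, not in a demonstrated miscalculation.

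**What to change.** In Sample Size Calculation, name the test and give the assumed effect as a between-arm difference in change in SD units. Replace the 95% claim with wording such as: 'With 40 participants analysed (20 per arm), a Time 1–Time 2 correlation of 0.5 and two-sided alpha 0.05, power is about 87% for a 1.0 SD between-arm difference in change, and about 34% (change score) to 43% (baseline-adjusted) for a 0.5 SD difference.' If a larger effect such as f = 0.30 was used, print it with its equivalent of 1.2 SD and do not call it medium. Add that about 38 are expected from 48 after 20% attrition, with power of about 85% for 1.0 SD.

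This is rewording only. It needs no added participants and no change to the primary measures. The one cost is a less favourable stated power.
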